# Forced diuresis with matched hydration in reducing acute kidney injury during transcatheter aortic valve implantation (Reduce-AKI): study protocol for a randomized sham-controlled trial

**DOI:** 10.1186/1745-6215-15-262

**Published:** 2014-07-02

## Abstract

**Background:**

Acute kidney injury (AKI) is observed in up to 41% of patients undergoing transcatheter aortic valve implantation (TAVI) and is associated with increased risk for mortality. The aim of the present study is to evaluate whether furosemide-induced diuresis with matched isotonic intravenous hydration using the RenalGuard system reduces AKI in patients undergoing TAVI.

**Methods/Design:**

Reduce-AKI is a randomized sham-controlled study designed to examine the effect of an automated matched hydration system in the prevention of AKI in patients undergoing TAVI. Patients will be randomized in a 1:1 fashion to the RenalGuard system (active group) versus non-matched saline infusion (sham-controlled group). Both arms receive standard overnight saline infusion and N-acetyl cysteine before the procedure.

**Discussion:**

The Reduce-AKI trial will investigate whether the use of automated forced diuresis with matched saline infusion is an effective therapeutic tool to reduce the occurrence of AKI in patients undergoing TAVI.

**Trial registration:**

Clinicaltrials.gov: NCT01866800, 30 April 30 2013.

## Background

Acute kidney injury (AKI) is a frequent complication of coronary angiography, and is associated with unfavorable outcomes including major cardiovascular events, renal replacement therapy, prolonged hospitalization, and early death [1,2]. Recently, two randomized controlled trials have demonstrated that furosemide-induced diuresis with matched isotonic intravenous hydration using the RenalGuard system (PLC Medical Systems, Milford, Massachusetts, USA) [3,4] reduces AKI in high-risk patients undergoing coronary procedures.

Elderly patients undergoing TAVI have a high prevalence of chronic kidney disease (CKD) and therefore are at increased risk to develop AKI (Table 1). In recent reports, AKI has been observed in up to 41% of patients undergoing TAVI [5-11] and was associated with a four times higher post-procedural mortality [11-14]. ‘RenalGuard’ is a Conformité Européenne (CE)-approved system that is being used worldwide. The objective of this randomized sham-controlled study is to assess the beneficial effect of treating TAVI patients with this system in reducing the occurrence of AKI.

**Table 1 T1:** **Definition of acute kidney injury post transcatheter aortic valve implantation (TAVI) according to the VARC-2 classification **[15]**]**

**Stage 1**	Increase in serum creatinine to 150 to 199% of baseline
	**OR**
	Increase of ≥0.3 mg/dl (26.4 mmol/L)
	**OR**
	Urine output <0.5 ml/kg/h for >6 but <12 h
**Stage 2**	Increase in serum creatinine to 200 to 299% of baseline
	**OR**
	Urine output <0.5 ml/kg/h for >2 but <24 h
**Stage 3**	Increase in serum creatinine to ≥300% of baseline
	**OR**
	Increase of serum creatinine of ≥4 mg/dL (354 mmol/L) with an acute increase of at least 0.5 mg/dl (44 mmol/l)
	**OR**
	Urine output <0.3 ml/kg/h for >24 h
	**OR**
	Anuria for >12 h

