### Primary endpoint

The primary endpoint is reduction of acute kidney injury (stage 1 or above) at 48 to 72 h. Serum creatinine level will be measured prior to TAVI and at 48 to 72 h post-procedure. AKI will be defined as stage 1, 2 or 3 according to VARC-2 AKI classification [15] (Table 1).

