## Discussion

The Reduce-AKI trial will investigate whether the use of forced diuresis with matched saline infusion using the RenalGuard system will reduce the occurrence of AKI in patients undergoing elective transfemoral TAVI.

AKI following TAVI is an independent predictor of short- and long-term outcome [6,11] In previously published studies, the incidence of AKI in patients undergoing TAVI ranged from 12% to 41% [6,9-11] with dialysis required in 1.5 to 10% [6,16].

The reasons for the increased risk of AKI in patients undergoing TAVI include elder population with multiple comorbidities, peri-procedural bleedings, hemodynamic instability, distal embolization and the use of nephrotoxic drugs.

Hydration is the cornerstone of AKI prevention. It increases the intravascular blood volume, suppresses the renin-angiotensin-aldosterone system, and promotes dilution and rapid evacuation of contrast media [4,9,17].

Furosemide may reduce the nephrotoxic effect of contrast media, first by increasing the urine flow and thus diluting the contrast media, and second by blocking tubular sodium reabsorption in the loop of Henle, thus reducing tubular workload and concomitant oxygen requirement.

The use of furosemide alone is controversial since it reduces the effective circulating volume and prostaglandin mediated vasodilation, and may lead to dehydration as a result of increased urine output [18,19]. However, when combining hydration with furosemide, studies have shown improved outcomes [3,4].

The RenalGuard system combines all the above methods for prevention of AKI and hydration with forced diuresis with furosemide, while preventing dehydration or fluid overload.

Recently, two randomized controlled trials [3,4] have demonstrated that furosemide-induced diuresis with matched isotonic intravenous hydration using the RenalGuard system reduces AKI in high-risk patients undergoing coronary procedures by up to 71%. In the present study, we chose to evaluate the effect of the RenalGuard system on patients with reduced eGFR since they are at the highest risk for AKI [6,7,20]. In most TAVI patients present with an eGFR below 60 ml/min/1.73 m2, the low eGFR is mostly due to their advanced age (above 80 years). The inclusion/exclusion criteria were very lenient in order to simulate ‘real life’ patients. Therefore, we believe that the Reduce-AKI study will demonstrate a reduction of AKI in this high-risk patient population.

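### Table 1 prints a Stage 2 urine-output window that contains Stage 1, so a literal reading lets a low-output spell of just over 2 h count as primary-endpoint AKI

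*Protocol article*

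**What the plan says.** The Primary endpoint section states: "The primary endpoint is reduction of acute kidney injury (stage 1 or above) at 48 to 72 h". It continues: "AKI will be defined as stage 1, 2 or 3 according to VARC-2 AKI classification", citing the source classification and Table 1 together. The only measurement named in that section is creatinine: "Serum creatinine level will be measured prior to TAVI and at 48 to 72 h post-procedure".

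Table 1 (Background) lists urine-output criteria as alternatives to the creatinine criteria in every stage:

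- Stage 1: "Urine output <0.5 ml/kg/h for >6 but <12 h"
- Stage 2: "Urine output <0.5 ml/kg/h for >2 but <24 h"
- Stage 3: "Urine output <0.3 ml/kg/h for >24 h", or anuria lasting more than 12 h

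Under Study protocol, the sham-group description says that the device records urine volume through the procedure and for 6 h after the last contrast dose. In the active group, furosemide is repeated when output is below 300 ml/h, up to a cumulative limit. The sham group receives no routine furosemide before the procedure.

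**The concern.** A staging scale should rise in severity and its stages should not overlap. Here Stages 1 and 2 share one urine threshold, yet the more severe stage needs the shorter spell. Because the endpoint is any stage, the Stage 2 row also sets the lowest urine-output entry to the primary endpoint.

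Two features of the design make this more than untidy staging. First, a spell of just over 2 h fits easily within the device's recording window. Second, the treatment acts directly on urine output: one arm is kept in forced diuresis and the other is not. A criterion met by brief low output would therefore pick up sham patients more often than active patients, and the error would favour the device.

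**Working it through.** **1. The plan's own figure.** The Power analysis gives 92 per group for 40% versus 20%, two-sided alpha 0.05 and 80% power. With pooled rate 0.30:

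n = [1.96·√(2·0.30·0.70) + 0.8416·√(0.40·0.60 + 0.20·0.80)]² / 0.20² = (1.270 + 0.532)² / 0.04 ≈ 81.2, so 82.

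With the continuity correction, n/4 · [1 + √(1 + 4/(n·0.20))]² ≈ 90.9, so 91. The stated 92 is consistent with this. The Table 1 row does not affect it, because the two rates are assumed inputs.

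**2. The windows side by side.** All spells are at output below 0.5 ml/kg/h, with the bounds as printed.

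| Spell | Stage 1 (6–12 h) | Stage 2 as printed (2–24 h) | Stage 2 if it began at 12 h |
|---|---|---|---|
| 2.1 h | no | yes | no |
| 4 h | no | yes | no |
| 6 h | no | yes | no |
| 8 h | yes | yes | no |
| 12.1 h | no | yes | yes |

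Every spell that meets Stage 1 also meets printed Stage 2. Spells of more than 2 h and up to 6 h are AKI only because of the printed Stage 2 row. Stage 1 ends at 12 h and the Stage 3 output row starts beyond 24 h, so the table's own sequence points to 12 h as the intended lower bound.

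**3. Observability and direction.** The stated recording window is the procedure plus 6 h after the last contrast dose. A spell of 2 to 6 h fits inside it. A spell of 12 h would not, unless more than 6 h of recording came before the last contrast dose. At an assumed body weight of 60 to 100 kg, 0.5 ml/kg/h is 30 to 50 ml/h. The 300 ml/h trigger in the active arm is therefore 6 to 10 times the oliguria threshold, so extra events would be expected mainly in the sham arm.

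**4. Size, if the printed row is applied.** Inputs from the plan: control AKI rate 40%, 110 per arm and 5% dropout (110 × 0.95 = 104.5, taken as 104). Assumptions: no true effect, and a fraction q of otherwise AKI-free patients reclassified in the sham arm only. The sham rate is then 0.40 + 0.60q and the active rate stays at 0.40. The chance of two-sided P<0.05 comes from exact binomial enumeration of the pooled z-test, which is equivalent to the uncorrected chi-square test.

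| q (assumed) | Sham rate | Active rate | Chance of P<0.05 |
|---|---|---|---|
| 0 | 40.0% | 40% | 5.2% |
| 2% | 41.2% | 40% | 5.6% |
| 5% | 43.0% | 40% | 7.4% |
| 10% | 46.0% | 40% | 14.0% |
| 20% | 52.0% | 40% | 39.9% |

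Nearly all of the excess lies on the side favouring the device. At q = 10%, 13.8 of the 14.0 percentage points do.

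**The case against.** The strongest reply is that this is a dropped digit in a table that summarises a named external classification, and that the classification governs. The Primary endpoint section names only creatinine, at 48 to 72 h, so a short spell in the first hours may never be adjudicated. In that case no event count changes. This reply stands as a limit on reach. It does not remove the point: the article cites Table 1 for the definition, prints the urine criteria as alternatives, and nowhere restricts the endpoint to creatinine or corrects the row.

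A reader might infer three stronger things that the documents do not support.

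- *That the trial is counting 2-hour spells as events.* Nothing shown says how adjudicators apply the urine criteria.
- *That the Stage 3 creatinine row also distorts the endpoint.* It reads "Increase of serum creatinine of ≥4 mg/dL (354 mmol/L) with an acute increase of at least 0.5 mg/dl (44 mmol/l"; as a rise, the first condition makes the second redundant, so a level was probably meant. Either reading already implies a rise of at least 0.3 mg/dl, which is Stage 1. An endpoint of any stage is unaffected, and the article specifies no stage-specific analysis.
- *That the lack of a dialysis row loses the worst cases.* The Discussion cites dialysis in 1.5 to 10% of patients, but does not say that it began before 48 h or that creatinine had normalised. Such patients would commonly qualify first by creatinine (sampled from 6 to 72 h) or by anuria, although the 48 to 72 h timing leaves some gap. A material power loss needs nearly all of them to be missed.

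**Conclusion.** The point holds as a wrong threshold in the table that defines the primary endpoint. As printed, Stage 2 contains Stage 1, and the shortest low-output spell that qualifies falls from more than 6 h to more than 2 h. That much follows from the document alone.

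The effect on results is conditional. It is nil if AKI is judged on creatinine alone or from the source classification. If the printed row is applied, the false-positive rate is close to nominal for a small sham-only excess (about 6% to 7% at 2% to 5%) and well above it for a larger one (about 14% at 10%, 40% at 20%). The documents give no figure for this excess, and the calculation also assumes none in the active arm. The direction, toward apparent benefit, rests on the arms' different urine management. The sample size is not affected.

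**What to change.** Reconcile the Stage 2 urine row with the cited VARC-2 classification so that it adjoins Stage 1. The table's sequence implies a lower bound of 12 h; the exact bound, and whether it is inclusive, should be taken from that source. Have the Clinical Event Committee, which the plan keeps blinded, confirm that any AKI already adjudicated on urine output in the 41 recruited patients used the corrected row.

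As a secondary wording point with no bearing on the primary endpoint, check the Stage 3 row on a 4 mg/dL increase against the same source.

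The cost is a table correction and a short review of existing records, with no new data and no change to the sample size. Doing it before unblinding avoids any later suggestion that the definition was changed after the results were seen.

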## Methods/Design

We describe a single-center, double-blinded, randomized sham-controlled trial that is being conducted at the Tel Aviv Medical Center, Tel Aviv, Israel.

### Transcatheter aortic valve implantation procedures

All patients will undergo transfemoral aortic valve implantation per standard clinical practice. Briefly, the femoral artery will be accessed with the standard endovascular technique, thereafter the procedure involves advancing a large catheter (18 Fr) through the aortic arch, retrogradely crossing the aortic valve, following by balloon valvuloplasty and stent-valve implantation. During the procedure, the patients will receive analgesics and anxiolytics as per protocol.

Post-procedural pharmacotherapy, sheath removal, and deployment of hemostatic devices will be left to the discretion of the attending cardiologists. Following treatment in the catheterization laboratory, medical treatment throughout hospitalization and follow-up treatment will be left to the discretion of the treating physician managing patient care on the hospital wards. Specific agents added or withdrawn will be made by treating physicians and will not be influenced by the study team.

### RenalGuard system

The RenalGuard system (PLC Medical Systems, Milford, Massachusetts, USA) is a CE approved system that is being used worldwide. It includes a computer system that weighs the urine of the patient, calculates the urine rate (ml/min) and infuses matched IV normal saline into the patient, maintaining the initially programmed fluid balance. In our medical center, the RenalGuard system is routinely used for high-risk patients undergoing coronary procedures (Figure 1).

**Figure 1 F1:**
[figure not shown]
The ‘RenalGuard’ system.

### Study population

A total of 220 patients will be randomized. Eligible patients must be planned for elective TAVI and all must have an estimated glomerular filtration rate (eGFR) below 60 ml/min/1.73 m^2^. We limited the number of inclusion and exclusion criteria in order to simulate real-life patients.

### Inclusion criteria

The inclusion criteria are as follows:

1. subject who is able and willing to give an informed consent is ≥65 years old,

2. is undergoing planned transfemoral TAVI due to severe aortic stenosis, and

3. has calculated eGFR below 60 ml/min/1.73 m2 (using Modification of Diet in Renal Disease (MDRD) formula).

### Exclusion criteria

The exclusion criteria are as follows:

1. history of acute coronary syndrome in the past 30 days,

2. history of congestive heart failure with left ventricular ejection fraction <30% or exacerbation in the past 30 days,

3. current dialysis treatment,

4. known furosemide hypersensitivity, or

5. contraindications to placement of a Foley catheter in the bladder.

### Randomization and blinding

At the time of enrollment, signed informed consent will be obtained as per the Tel Aviv Medical Center institutional ethical board standards. After signing the informed consent, patients will be randomized in a 1:1 fashion using closed envelopes. They will be randomized to the active use of RenalGuard system versus using passive use of the RenalGuard system using normal saline 0.9% infusion (sham-controlled group) (Figure 2). The RenalGuard system will be covered before, during and after the procedure with a bag in order to allow effective blinding. All participants will remain blinded throughout the 6-month study period. The interventional cardiologist conducting the TAVI procedure is also blinded to the study treatment arm. The supervising physician, core labs, the biostatisticians performing the analysis, the members of the Clinical Event Committee (CEC), as well as the members of the Data Safety Monitoring Board (DSMB) are blinded to treatment assignment until study completion and after the database has been unlocked.

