### Study protocol

#### Pre-procedural evaluation

After enrollment, patients will undergo the following baseline procedures: physical examination and medical interview; cardiac echocardiogram assessing systolic and diastolic function, as well as valvular function; endothelial function using the EndoPat™ system, a non-invasive method for assessing endothelial function; carotid artery ultrasound and doppler including Intima Media Thickness calculations; and blood and urine analysis as described below.

All participating patients will receive a standard pre-procedural hydration treatment plan consisting of an infusion of isotonic saline at a rate of 0.5 to 1 mL/kg per hour, starting 12 h prior to the procedure and continuing for 12 h after contrast administration. In addition, 1,200 mg of N-acetyl-cysteine will be administered orally twice daily the day before and the day of the procedure.

Each patient will be randomized to one of the following treatment strategies:

**Group 1** - Sham-controlled Group (Figure 3A). The patients will be connected to the RenalGuard System that will not be activated (passive mode).

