**Figure 3 F3:**
[figure not shown]
Treatment algorithms of the sham-controlled/passive RenalGuard group (group A) and the active RenalGuard group (group B).

Before the procedure: A standard 18 to 22 gauge catheter will be inserted into a peripheral vein of the arm and a standard Foley catheter will be placed in the bladder for urine collection (as performed routinely for all TAVI procedures). The intravenous (IV) line and the urinary catheter will be connected to the RenalGuard System. The RenalGuard System will be set to 0% match; that is, the urine rate and volume will be measured, but it will not deliver matched IV normal saline. The system will be computed to deliver continues IV normal saline at a rate of 100 cc/h (100 cc/h is the routine average fluid infusion rate in TAVI procedure) during the procedure and up to 6 h after the procedure. Neither a routine IV bolus of saline nor a routine IV furosemide will be given before the procedure.

During the procedure: The urine and infusion volumes will be measured by the RenalGuard system throughout the catheterization procedure and for 6 h after the last contrast dose. Additional IV fluids can be added as needed according to the clinical decision of the anesthesiologist or the attending physician.

We will analyze the quantity and quality of urine during the duration of the procedure.

**Group 2** - Active Group (Figure 3B). Treatment as group 1 and in addition, the RenalGuard system will be activated (active mode).

Before the procedure: A standard 18 to 22 gauge catheter will be inserted into a peripheral vein of the arm and a standard Foley catheter will be placed in the bladder for urine collection (as performed routinely for all TAVI procedures). The IV line and the urinary catheter will be connected to the RenalGuard System. The RenalGuard System will be set to 100% match; that is, the urine rate and volume will be measured and the system will deliver volume of IV normal saline that is matched to the volume of urine produced by the patient. An initial IV bolus (250 ml) of normal saline over 30 min will be administered approximately 90 min before the procedure; in patients with heart failure, the volume of the bolus can be reduced to 150 ml. Furosemide will then be administered as a single intravenous bolus of 0.25 to 0.5 mg/kg at the physician’s discretion. When a urine output rate >300 ml/h will be achieved, the patients will be sent to the catheterization laboratory.

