### Power analysis

The study is powered to detect a 50% reduction in AKI between the groups. The following assumptions and hypotheses correspond to the primary objective:

A = 40% of participants in the sham-controlled group will develop AKI.

B = 20% of participants in the active group will develop AKI.

Hypotheses:

H0: A = B

H1: A ≠ B

Type I error rate = 5% (2-sided) with power = 80%

Drop out/lost to follow –up, rate = 5%

Under the assumption that AKI is relatively common (40%) after TAVI, and that the RenalGuard system has been shown to reduce the incidence of AKI by up to 70% [3,4], we estimated that if there will be a 50% reduction in AKI in the RenalGuard group, the number of patients needed in each group to attain 80% power with an alpha of 0.05, is 92. We plan on recruiting 110 patients in each group (220 total) in order to assure achieving statistical power.

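### The plan does not fix when the envelope is opened; its wording permits, and probably implies, allocation before the work-up and pre-procedural saline, earlier than any arm-specific step requires

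*Protocol article*

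**What the plan says.** Two sections of the protocol article describe the order of events.

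- **Randomization and blinding.** "At the time of enrollment, signed informed consent will be obtained", and then: "After signing the informed consent, patients will be randomized", 1:1 by closed envelope. Participants, the operator, the supervising physician, core labs, biostatisticians, event committee and safety board are listed as blinded. The staff who open the envelope, run the console or set the overnight infusion are not mentioned.
- **Pre-procedural evaluation.** "After enrollment, patients will undergo the following baseline procedures": examination, echocardiogram, endothelial function, carotid ultrasound, blood and urine. All patients then receive "an infusion of isotonic saline at a rate of 0.5 to 1 mL/kg per hour", from 12 h before the procedure until 12 h after contrast. Only after this text does the section say: "Each patient will be randomized to one of the following treatment strategies".

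The group descriptions that follow give both arms the same venous line and Foley catheter, and for both: "The intravenous (IV) line and the urinary catheter will be connected to the RenalGuard System". The arms part at the next step, when the match is set to 0% or 100%. The active arm then has a saline bolus about 90 min before the procedure, followed by furosemide.

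The primary endpoint compares creatinine before TAVI with creatinine 48 to 72 h after it (Primary endpoint). It is analysed by intention to treat (Statistical analysis).

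**The concern.** If the envelope is opened at enrolment, allocation precedes the need for it by at least the 12 h of saline plus the work-up. Two avoidable problems follow.

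1. **Randomised patients without an outcome.** A patient whose TAVI is cancelled after allocation stays in the intention-to-treat set but cannot have a post-procedure creatinine. The protocol foresees such patients, because its per-protocol set is limited to those who completed the procedure. The echocardiogram also comes after enrolment, while an ejection fraction below 30% is part of an exclusion criterion. That criterion is worded as history, but a disqualifying value could still surface after allocation.
2. **A co-intervention open to influence.** The saline rate may be chosen within a twofold range, and no rule for choosing is given. The Discussion treats hydration as central to preventing AKI. Someone who knows the arm and sets the rate could, knowingly or not, hydrate the arms differently.

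**Working it through.** **Order of events.** Consent is at enrolment and randomisation follows consent; the work-up follows enrolment. Tying allocation to consent makes enrolment the natural moment for it, before the work-up and saline. The second mention of randomisation, placed after the hydration text, also fits the sequence consent, work-up, saline, envelope. The two sections can therefore be read consistently, but they do not fix the moment.

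**When allocation is first needed.** Saline and N-acetyl cysteine are common to both arms, as are line, catheter and console. The first arm-specific act is the match setting; the first with a stated time is the bolus about 90 min before TAVI.

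**Inputs for power** (Power analysis): AKI 40% and 20%, two-sided alpha 5%, power 80%, loss 5%, 92 needed and 110 planned per arm.

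**The plan's own figure.** With d = 0.20 and mean rate 0.30:

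n = [1.960√(2 × 0.30 × 0.70) + 0.842√(0.24 + 0.16)]² / 0.20² = 81.2, so 82.

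The continuity correction, n/4 × [1 + √(1 + 4/(nd))]², gives 90.9 (so 91) from 81.2, and 91.7 (so 92) from the rounded 82. The stated 92 is reproduced.

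**Power at 110 per arm**, without continuity correction:

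Power = Φ{[d − 1.960√(2p̄(1 − p̄)/n)] / √([pA(1 − pA) + pB(1 − pB)]/n)}

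- No loss: (0.20 − 0.1211)/0.0603 = 1.308, power 90.5% (87.6% with continuity correction).
- The stated 5% is 0.05 × 220 = 11 patients. If all are lost before TAVI and counted as no AKI, the rates are 0.95 × 40% = 38% and 0.95 × 20% = 19%: (0.19 − 0.1193)/0.0595 = 1.188, power 88.3%.

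No cancellation rate is given, so the share lost before TAVI is assumed equal in both arms and varied:

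| Lost before TAVI | Left out of analysis | Counted as non-events | Counted as events |
|---|---|---|---|
| 5% | 89.0% | 88.3% | 85.2% |
| 10% | 87.2% | 85.7% | 79.4% |
| 20% | 83.1% | 79.8% | 66.9% |

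The step from 92 to 110 absorbs 1 − 92/110 = 16.4% loss per arm.

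**Discretion in pre-procedural saline.** At an assumed 70 kg, 0.5 × 70 × 12 = 420 mL and 1 × 70 × 12 = 840 mL, a spread of 420 mL (360 mL at 60 kg, 480 mL at 80 kg). The active-arm bolus is 250 ml. The spread is the width of the permitted range; it does not estimate a difference between arms.

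**The case against.** The strongest reply is that the protocol fixes a sequence (consent, then allocation) and no interval. Late randomisation satisfies both sections, and the flow chart, which could not be seen, may show the order. This stands as far as it goes. A reader might infer that patients are randomised immediately after consent, or that the two sections contradict each other. The text states neither. It leaves the timing open and leans towards early.

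A reader might also infer that overnight hydration will be biased. That needs both allocation more than 12 h before TAVI and a person aware of the arm setting the rate. The documents neither state nor exclude this. Any effect on the baseline endothelial and carotid tests matters less still, because under Secondary endpoints these serve as predictors of AKI, not as comparisons between arms.

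How patients without an outcome are handled commonly belongs in the statistical analysis plan, which is not at hand, so the absence of a rule is not a fault here. The point is that later allocation keeps such patients from arising.

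Finally, the infusion runs until 12 h after contrast and extra fluids are allowed in both arms, so a later envelope removes only part of the discretion. That is correct: the change protects the choice of rate before the procedure and nothing after it.

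**Conclusion.** The point holds as a minor design matter. The sections permit, and probably imply, allocation before the work-up and pre-procedural saline, with no treatment reason for it. Allocating at console connection would keep out of the randomised set every patient whose TAVI is cancelled before then. It would also shield the baseline tests and the initial saline rate from knowledge of the arm.

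The size is small. With 5% lost before TAVI and counted as non-events, power goes from 90.5% to 88.3%, above the 80% planned. It falls below 80% only under heavier assumptions: about 10% lost and all counted as events, or about 20% lost and counted as non-events. These figures rest on the protocol's 40% and 20%, equal loss in both arms, and an assumed cancellation rate. The required sample size does not change. The influence on saline rate is a possibility the wording leaves open, and its effect on AKI cannot be quantified from the documents.

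**What to change.** Reconcile Randomization and blinding with Pre-procedural evaluation by one statement of timing. The next envelope is opened on the procedure day, once the venous line and Foley catheter are connected to the console, and before the match setting or any other arm-specific step. By then the baseline tests are done and the pre-procedural saline rate has been chosen and recorded. The infusion continues after allocation as the protocol describes, and no dose or rate is altered.

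The cost is a wording amendment and having the envelope available on the procedure morning. With 41 of 220 patients recruited when the article was written, the change could still have covered the remaining 220 − 41 = 179.

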### Safety

The RenalGuard system is approved for coronary angiography. Since all patients undergoing TAVI undergo urinary catheterization with a Foley catheter, our major safety issue is related to fluid overload. We will assess this issue by evaluating both in-hospital and 30-day readmission rate for congestive heart failure exacerbation, using patient medical records and medical interviews. In addition, we will evaluate all other safety criteria according to the VARC-2 criteria for TAVI procedures [15].

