### Interim analysis

An independent DSMB is chartered to monitor and evaluate patient safety to identify any clinically relevant trends, and to recommend whether the study should continue. The DSMB review will occur after 30 randomized patients have completed the 30-day follow-up and after approximately 25%, 50%, and 75% of the cohort has completed their six-month follow-up. An interim analysis for efficacy is planned after 50% of the cohort is enrolled.

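### The DSMB is blinded to treatment assignment until study completion, with no exception for interim review, so it could not learn which arm carries a safety excess it is charged to detect

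*Protocol article*

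**What the plan says.** Three sections of the protocol article bear on this point.

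- **Randomization and blinding** lists those who stay blinded: the supervising physician, core labs, the biostatisticians performing the analysis, the Clinical Event Committee (CEC), "as well as the members of the Data Safety Monitoring Board (DSMB) are blinded to treatment assignment until study completion". The sentence has no carve-out for interim review.
- **Interim analysis** charges the same board "to identify any clinically relevant trends, and to recommend whether the study should continue". Four reviews are set. The first is defined as "The DSMB review will occur after 30 randomized patients have completed the 30-day follow-up". The others follow when about 25%, 50% and 75% of the cohort have reached six months. The section then adds: "An interim analysis for efficacy is planned after 50% of the cohort is enrolled". It does not say who conducts or judges that analysis.
- **Safety** states that "our major safety issue is related to fluid overload", to be assessed by "evaluating both in-hospital and 30-day readmission rate for congestive heart failure exacerbation".

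**The concern.** The board's task is comparative. The enrolled patients are at least 65 years old, with severe aortic stenosis and reduced eGFR, so some heart-failure exacerbation is to be expected in both arms. Only the active arm receives the initial saline bolus, furosemide and urine-matched infusion. Whether events come from this treatment or from background risk can be judged only by comparing the arms, and acted on sensibly only if the board can find out which arm is which.

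The blinding rule withholds that until the study is over. The analysing biostatisticians fall under the same rule, so the article names nobody who could prepare or interpret interim data by identified arm. What is at stake is the protection of patients during the trial. The validity of the final primary comparison is not affected.

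**Working it through.** The plan contains no figure to reproduce on this point. The check sets the stated rules against each other, and an illustration then shows what each kind of report would reveal.

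**Step 1: the rules side by side.** Duty: find safety trends and recommend on continuation, at four reviews. Main hazard: fluid overload, measured by heart-failure exacerbation. Access: no knowledge of treatment assignment until study completion. The access rule allows two kinds of report, pooled or split by coded arm.

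**Step 2: inputs for the illustration.** The planned total is 220 with 1:1 allocation (Power analysis; Randomization and blinding). Half of the cohort is 0.50 × 220 = 110, or 55 per arm. The documents give no heart-failure rate, so all event counts below are assumed.

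**Step 3: pooled report.** Take 14 events in 110, 14/110 = 12.7%.

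- Split 7 versus 7: difference 0, P = 1.00.
- Split 11 versus 3: 11/55 = 20.0% and 3/55 = 5.5%, difference 8/55 = 0.1455.
  - Standard error = √[0.1273 × 0.8727 × (2/55)] = 0.0636.
  - z = 0.1455/0.0636 = 2.29, two-sided P = 0.022.
  - With a cell as small as 3, Fisher's exact test is the safer figure: P = 0.042. The continuity-corrected chi-square gives P = 0.045.

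The pooled line is the same in both cases.

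**Step 4: other assumed counts.** Eleven events in 110 (10%) give the same picture:

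| Split (55 per arm) | Pooled | Fisher P |
|---|---|---|
| 5 vs 6 | 11/110 | 1.00 |
| 2 vs 9 | 11/110 | 0.052 |
| 1 vs 10 | 11/110 | 0.008 |

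**Step 5: coded report.** A table by arm X and arm Y would show 11 versus 3, so the imbalance is visible. The two-sided P value is the same whichever code is the active arm. More heart failure under active treatment counts against the intervention, and more under sham counts in its favour. The same ambiguity applies to any AKI difference, so harm and benefit cannot be weighed by identified treatment.

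**Step 6: efficacy interim.** A two-sided comparison of AKI can be computed on coded arms. The article names no one to judge it, and the analysing biostatisticians are blinded.

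**The case against.** The strongest reply is that being blinded to assignment does not mean seeing pooled data only. Coded reports fit the wording and would show an imbalance. This stands. A reader might infer that the board cannot see a fluid-overload imbalance at all, or that the safety review could not work. The article does not support that, because it neither provides for coded reports nor excludes them. A board that saw a coded imbalance, or a run of serious cases, could still recommend a pause or ask for more information. What it lacks under the stated rule is a way to learn the direction before the study ends.

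A second reply is that report format and unmasking belong in the board's charter, which is not shown. For report format this is fair, and its absence from the article is no fault. It does not dispose of the blinding rule, which is stated outright: a charter that let the board unmask would contradict it.

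A third reply concerns the efficacy interim. A reader might infer that the board has to judge it and cannot. The sentence stands in the paragraph on the board but does not assign the analysis to it. The blinding rule also does not rule out a separate independent statistician. Only the narrower point remains: the article does not name who judges it.

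Finally, the device matches infusion to urine output to hold a programmed fluid balance, and patients with recent heart-failure exacerbation, or heart failure with a very low ejection fraction, are excluded. Both may lower the risk, but the article itself still calls fluid overload its major safety issue.

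**Conclusion.** The point holds in a limited form. The unqualified blinding of the board until study completion conflicts with its duty to act on safety trends. It leaves the board with pooled data or, at best, a coded split whose direction it may not learn in time.

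The size can only be illustrated. With 55 patients per arm, one pooled count of 14 covers anything from no difference to 11 versus 3 (Fisher P about 0.04; the uncorrected z-test P of about 0.02 is the more favourable figure). These counts are assumptions and forecast nothing. The conclusion does not depend on them, because it follows from the two rules. The point should be corrected, but it does not invalidate the primary analysis.

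**What to change.** 1. In Randomization and blinding, take the DSMB out of the group blinded until study completion. Investigators, the CEC, core labs and the final-analysis statisticians stay blinded.
2. In Interim analysis, state that at each review the board receives a confidential closed report by arm, coded, with a key that it may open at its discretion. Someone outside the blinded study team should prepare it, for example a statistician given the allocation list by its holder.
3. In the same section, state who conducts and who judges the efficacy interim.
4. Bring the board's charter into line.

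The cost is protocol and charter wording plus one table by arm per review. The small downside is that board members will know interim comparative results, which confidentiality handles. The change was still timely at publication: 41 patients had been recruited, fewer than the 55 (25% of 220) needed for the first six-month review, so the three six-month reviews and the efficacy interim lay ahead.
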